### Study outcomes

Primary outcomes include patient reported symptom burden and organ injury metrics as assessed by functional performance evaluations, serum biomarkers and MRI tissue characterization (Table 1). Secondary outcomes include imaging and circulating biomarkers of cardiovascular health (Table 2). Clinical events at 12 months will be collected though chart review to ascertain relevant clinical outcomes including incident diabetes and cardiovascular disease.

**Table 1 tab1:** Summary of organ injury outcomes.

Organ	Functional performance	Circulating biomarkers	Magnetic resonance
LUNG	Spirometry 6 min walk testing	None	Lung water density Lung lesions (radiomic analysis)
CARDIAC	6 min walk testing	Troponin I B-type natriuretic peptide	LVEF Myocardial T1 Myocardial T2
BRAIN	Cognitive testing	None	Brain volume Brain lesions (FLAIR and DTI) Susceptibility and iron mapping
HEPATIC	None	AST ALT GGT LDH Total bilirubin	Hepatic T1 Hepatic T2*
RENAL	None	Electrolytes Creatinine	Renal T1
SKELETAL MUSCLE	6 min walk testing	None	Skeletal muscle T1 Skeletal muscle T2*

AST, aspartate aminotransferase; ALT, alanine aminotransferase; LDH, lactate dehydrogenase; GGT, gamma-glutamyl transferase; LVEF, left ventricular ejection fraction; FLAIR, fluid attenuation inversion recovery; DTI, diffusion tensor imaging.

**Table 2 tab2:** Summary of cardiovascular health outcomes.

	Circulating biomarkers	Magnetic resonance	Clinical events
CARDIAC	Troponin I B-type natriuretic peptide	LVEF Myocardial T1 Myocardial T2	Cardiovascular death or hospitalization
CARDIOMETABOLIC	C-reactive protein White blood cell count Glucose Insulin Lipid profile	Visceral adipose tissue Hepatic fat Intramuscular fat Intermuscular fat	Incident diabetes Incident dyslipidemia Incident hypertension

LVEF, left ventricular ejection fraction.

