*Brain*: After repositioning the participant into a 64 channel head RF coil, four different images were acquired of the brain over 24 min: (i) 3D fluid attenuation inversion recovery (FLAIR) for lesion detection (1.0 mm isotropic, 5 min), (ii) 3D T1-weighted MPRAGE for regional brain volumes (0.85 mm isotropic, 3.5 min), (iii) 2D high-resolution diffusion tensor imaging (DTI) for identifying strokes/cytotoxic edema and microstructure in white matter mainly (1.5 mm isotropic, 10 b0/6 b500/20 b1000/64 b2500 s/mm^2^, 9.5 min), and 3D multi-echo, gradient recalled echo (0.9 × 0.9 × 1.7 mm^3^, 6 TE from 3.8–31 ms, 5.5 min) for quantitative susceptibility mapping (QSM) and transverse relaxation rate (R2*) for micro-bleeds and sensitivity to iron/myelin, particularly in deep gray matter. The latter three images match previous protocols of a healthy cohort (19).

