### Statistical plan

The Shapiro–Wilk normality test will be used to test the normal distribution of continuous variables which will be expressed as mean ± standard deviation or median (25th, 75th percentile), as appropriate. Categorical variables will be expressed as frequency and percentage. When comparing data between recovered COVID-19 patients and healthy controls, chi-square testing or Fisher’s exact test will be used for categorical variables and two sample t-test or Mann–Whitney U test used for continuous variables, as appropriate. Functional performance, biomarker results and imaging metrics indicative of organ injury will be compared across groups of symptom severity (none, mild, moderate and severe) within the recovered COVID-19 patients using a one-way analysis of variance with *post hoc* pairwise comparisons by either Tukey’s or Games-Howell tests, depending on equality of variances. Pearson correlation analyses will evaluate relationships between MRI measures of tissue injury and functional performance metrics. Univariable Cox proportional regression of clinical outcome will be performed in all serum and imaging parameters. In the multivariable Cox proportional hazard analysis, all non-collinear parameters of interest with univariable *p*-value < 0.2 will independently test for their association with composite outcome after adjustment for baseline risk. A *p* value less than 0.05 will be considered significant for all tests.

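### Brain volume is a primary injury metric analysed with covariate-free tests, and the article names no head-size normalisation

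*Protocol article*

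**What the plan says.** Study outcomes in the protocol article sets the status of the metric: "Primary outcomes include patient reported symptom burden and organ injury metrics as assessed by functional performance evaluations, serum biomarkers and MRI tissue characterization (Table 1". The brain row of Table 1 gives its MRI metrics as "Brain volume Brain lesions (FLAIR and DTI) Susceptibility and iron mapping". The Brain paragraph under Magnetic resonance imaging describes the source scan as "3D T1-weighted MPRAGE for regional brain volumes". It covers acquisition only, with no segmentation or derivation step.

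The Statistical plan names three analyses that would apply to this metric:

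- Patients versus controls: "two sample t-test or Mann–Whitney U test used for continuous variables, as appropriate".
- Across symptom-severity groups within patients: one-way ANOVA, with "pairwise comparisons by either Tukey’s or Games-Howell tests, depending on equality of variances".
- Against function, which for the brain row means cognitive testing: Pearson correlation of "relationships between MRI measures of tissue injury and functional performance metrics".

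The threshold is common to all: a p "value less than 0.05 will be considered significant for all tests". Adjustment appears only in the multivariable Cox model for clinical outcome. Intracranial volume and head size are not mentioned anywhere in the article.

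On the comparison group, Study design and Sample size calculation call the controls age- and sex-matched. Table 3 shows 139/215 versus 68/133 female, mean height 168 versus 170 cm and mean age 51 versus 47 years. Participant selection says the normative brain imaging and cognitive testing came from healthy controls studied separately before the pandemic. Their number, sex mix, age and height are not given.

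**The concern.** Brain volume is the only MRI entry in Table 1 that is the size of an organ. The others are relaxation times, a density, an ejection fraction, susceptibility or lesions. Size carries head scale with it. Each participant is imaged at one visit, so no within-person change is available to cancel lifelong head size.

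Two things are at stake if unscaled volumes go into the stated tests. The first is precision: variance due to head size adds noise to the group comparisons and pulls the correlation with cognition towards zero. The second is bias: if the groups differ in sex mix or stature, part of a volume difference would be head size and could be read as injury, in either direction.

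**Working it through.** **No plan figure to reproduce.** The target of 200 patients and 100 controls is described as empirical, with no effect size, SD or power behind it. The Table 3 sex percentages can be checked: 139/215 = 64.7% and 68/133 = 51.1%, matching the printed 65% and 51%.

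**Inputs from the article.** 215 patients; 133 controls; significance level 0.05, taken as two-sided because sidedness is not stated.

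**Assumptions not in the documents.** Raw brain volume has an SD of 10% of its mean. Head size explains a share R² of its variance, varied from 0.3 to 0.8. Head size is unaffected by disease and unrelated to cognition. The brain comparison has 133 controls, although the size of the pre-pandemic brain set is not reported. Men's brains are 8 to 12% larger on average.

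**1. Power of the patient–control comparison.**

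SE (unscaled) = 10 × √(1/133 + 1/215) = 10 × 0.1103 = 1.103% of the mean. After normalisation, SE is multiplied by √(1 − R²). Power = Φ(loss/SE − 1.96).

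For a 2% loss, unscaled: 2/1.103 = 1.813, so power = Φ(−0.147) = 44%. With R² = 0.5: 1.813/0.707 = 2.564, so power = Φ(0.604) = 73%.

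| True loss | Unscaled | Normalised, R² 0.3 | R² 0.5 | R² 0.8 |
|---|---|---|---|---|
| 1% | 15% | 19% | 25% | 53% |
| 2% | 44% | 58% | 73% | 98% |
| 3% | 78% | 90% | 97% | >99% |

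**2. Correlation with cognition, n = 215.**

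If normalised volume has true correlation ρ with a test score, unscaled volume has correlation ρ√(1 − R²). Power = Φ(atanh(r) × √212 − 1.96). For ρ = 0.3, power on normalised volume is 99.5%. On unscaled volume:

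| R² | Attenuated r | Power |
|---|---|---|
| 0.3 | 0.25 | 96% |
| 0.5 | 0.21 | 88% |
| 0.8 | 0.13 | 50% |

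**3. Possible bias from sex mix.**

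Difference in female share = 64.7% − 51.1% = 13.5 points from unrounded values (z = 2.50, p = 0.013). Apparent deficit in patients with no disease effect = 0.135 × 8% = 1.1%, up to 0.135 × 12% = 1.6%. At SE 1.103%, the chance of a significant result in the direction of loss is Φ(1.08/1.103 − 1.96) = 16%, up to Φ(1.62/1.103 − 1.96) = 31%. This applies only if the separate brain controls have Table 3's sex mix, which the article does not say.

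**4. Age.** The Table 3 difference is 4 years, with SE √(14²/215 + 15²/133) = 1.61 and t = 2.48. Head-size scaling is not an adjustment for age, so age needs its own term.

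**The case against.** The strongest objection is that the article never says unscaled volume will be analysed. It is a condensed account, and for the brain it leaves out post-processing altogether, whereas it gives derivation steps for liver, kidney, muscle and lung. Head-size scaling belongs to that omitted step and may sit in a full protocol, imaging manual or analysis plan. Covariate-free tests do not settle the matter either: if volume is scaled when it is derived, a t-test or Pearson correlation on the result needs no further head-size term. This stands. A reader might infer that the sponsor has chosen raw volume, but the documents show only that no normalisation is mentioned.

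A reader might also infer that most of the variation in brain volume is skull size, so that true loss or a link with cognition is largely buried. The article gives no mean, SD or correlation with intracranial volume to support that. Assuming correlations of 0.8, 0.9 and 0.95, an effect with 80% power after normalisation would have 39%, 23% and 14% without it. That range covers only strong correlations, and regional volumes may sit lower. At milder values the loss is modest, as the tables above show.

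The wording in Table 1 and the phrase "3D T1-weighted MPRAGE for regional brain volumes (0.85 mm isotropic, 3.5 min" are not in conflict: a short table label can cover regional volumes. It does leave open which volumes are the outcome.

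Finally, brain volume is one of many MRI entries and no sample-size calculation rests on it. That limits the weight of the point but does not remove it, because the metric is primary.

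**Conclusion.** The point holds as a conditional one. The article names brain volume as a primary injury metric, fixes covariate-free tests and states no head-size normalisation. If those tests are run on unscaled volumes, head size is mixed with injury.

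Under the assumed 10% SD and 215 versus 133, the cost for a 2% loss runs from mild (58% power down to 44% at R² 0.3) to severe (98% down to 44% at R² 0.8). A 3% loss remains reasonably detectable at 78%. A spurious deficit of about 1.1 to 1.6% is possible if the brain controls share Table 3's sex mix and the assumed sex difference applies; with another mix it could be smaller, larger or reversed. The documents support neither the claim that raw volume is the chosen measure nor the claim that real effects would generally be hidden.

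**What to change.** In Table 1, replace the brain volume entry with total brain volume and a named list of regional volumes, each adjusted for intracranial volume estimated from the same MPRAGE, either as a covariate or by the residual method. In the Statistical plan, carry that adjustment together with age and sex into the patient–control comparison, the symptom-group comparison and the correlations with cognitive testing, using a linear model and partial correlations. Report the number, age and sex mix of the pre-pandemic brain controls.

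The cost is one further segmentation output from a scan already acquired and three model terms. The analyses are still described in the future tense. If normalisation is already specified elsewhere, one sentence saying so settles the head-size part; the age and sex terms would still need stating.

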**Figure 1 fig1:**
[figure not shown]
Schema of study design. Upper panel depicts recruitment of patients with recovered COVID-19 and healthy controls without prior COVID-19. Middle panel depicts functional testing, blood collection and magnetic resonance imaging for all participants. Functional testing included Brief Smell Identification Testing (B-SIT), 6 min walk testing, cognitive testing on a tablet with NIH toolbox and spirometry. Bottom panel depicts collection of clinical outcomes at 12 months. CBC, complete blood count; AST, aspartate aminotransferase; ALT, alanine aminotransferase; LDH, lactate dehydrogenase; GGT, gamma-glutamyl transferase; LVEF, left ventricular ejection fraction; DTI, diffusion tensor imaging.

A detailed assessment of relevant medical history and medication use was achieved through direct questioning and a review of health records. In patients with recovered COVID-19, data on the timing and duration of illness, the need for hospitalization and transfer to intensive care were recorded.

At the time of study-related functional assessments and MRI, patients with recovered COVID-19 were screened for the presence of long COVID related symptoms including fatigue, cognitive impairment, shortness of breath, chest pain and palpitations using a standardized questionnaire. Additionally, patients rated the overall impact of these symptoms on their daily activities using a 5-point scale ranging from 1 (no limitations) to 5 (severely limited).

Blood pressure, heart rate and oxygen saturation were measured on all participants and blood work was performed to assess for circulating biomarkers of inflammation (c-reactive protein, white blood cell count with differential and d-dimer), end organ damage (high sensitivity cardiac troponin I, b-type natriuretic peptide, creatinine and hepatic enzymes) and cardiometabolic profile (glucose, insulin and lipid profile). Blood biospecimens were also stored in a research biobank (Canadian BioSample Repository) for future analysis.

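### Table 1 lists LDH as a liver-only marker and electrolytes and raw creatinine as kidney injury markers, so a group difference can be assigned to the wrong organ or a renal difference masked

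*Protocol article*

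**What the plan says.** The Study outcomes section of the protocol article states: "Primary outcomes include patient reported symptom burden and organ injury metrics as assessed by functional performance evaluations, serum biomarkers and MRI tissue characterization". It refers to Table 1, which assigns each measure to an organ.

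- **Hepatic row:** the circulating biomarkers are "AST ALT GGT LDH Total bilirubin", beside the MRI metrics "Hepatic T1 Hepatic T2" (the second with its asterisk).
- **Renal row:** the circulating biomarkers are "Electrolytes Creatinine", beside renal T1.
- **Lung and skeletal muscle rows:** the circulating-biomarker cell reads None.

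The section on medical profile, symptoms and blood collection describes the markers of "end organ damage (high sensitivity cardiac troponin I, b-type natriuretic peptide, creatinine and hepatic enzymes". Electrolytes are not in that list. No indexed or estimated measure of kidney function appears in the article.

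For patients against controls, the Statistical plan specifies a "two sample t-test or Mann–Whitney U test used for continuous variables, as appropriate". Across symptom-severity groups it compares the metrics "using a one-way analysis of variance with" post hoc pairwise tests. It also sets a p "value less than 0.05 will be considered significant for all tests". Adjustment for baseline risk is mentioned only for the multivariable Cox model.

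**The concern.** The study sets out to say which organs are injured after COVID-19, so a marker listed under one organ should mainly reflect that organ. Three entries do not.

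- **LDH** is released by lung, muscle and red cells as well as liver. Lung and muscle are two of the organs under study, and both are shown as having no blood marker. Table 1 does let one measure serve several organs: the 6 min walk test stands in the lung, cardiac and skeletal muscle rows. LDH stands in one row only.
- **Electrolytes** respond to many influences and are not a specific measure of kidney injury.
- **Raw creatinine** varies with sex and muscle mass as well as with filtration. The planned two-group test does not allow for either.

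At stake is how a primary, organ-specific comparison is read. Residual lung or muscle damage could appear under the liver heading, and a real renal difference could be partly cancelled by a difference in who is in the two groups.

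**Working it through.** The article states no power, effect size or SD for these markers, and its target of 200 patients and 100 controls is described as empirical. There is no stated figure to reproduce. The check has two parts: whether the groups differ on determinants of creatinine, and how large the resulting shift could be.

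**1. Imbalance, from Table 3 (215 patients, 133 controls)**

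- Sex: 139/215 = 64.7% and 68/133 = 51.1% women, a difference of 13.5 points. Pearson chi-square without continuity correction is 6.24, p = 0.013; Fisher's exact p = 0.014.
- Age: 51 (SD 14) against 47 (SD 15) years. SE = √(14²/215 + 15²/133) = 1.61; t = 4/1.61 = 2.48, p = 0.014.
- Weight: 83 (SD 20) against 72 (SD 13) kg. SE = √(20²/215 + 13²/133) = 1.77; t = 11/1.77 = 6.22, p < 0.001. Standardised difference = 11/√((20² + 13²)/2) = 0.65.

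So the groups differ in sex and age although the Study design section calls the controls age- and sex-matched. They also differ in weight.

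**2. Effect of the sex mix on an unadjusted creatinine comparison**

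Assumptions, not in the document: creatinine is 10 to 20 µmol/L higher in men than in women, the within-sex SD is 10 to 15 µmol/L, and the test is two-sided at 5% with a normal approximation.

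- Shift in the patients' mean = −(difference in share of women) × gap. This gives −0.135 × 10 = −1.4 and −0.135 × 20 = −2.7 µmol/L, with no difference in kidney function.
- Overall SD = √(within-sex SD² + p(1 − p) × gap²), where p = 207/348 = 0.595.
- SE = overall SD × √(1/215 + 1/133) = overall SD × 0.110.

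Power to detect a true rise of 5 µmol/L in patients, at the two ends of the range:

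| Gap / within-sex SD (µmol/L) | SE | Shift | Power without shift | Power with shift |
|---|---|---|---|---|
| 10 / 10 | 1.23 | −1.4 | 98% | 84% |
| 20 / 15 | 1.98 | −2.7 | 72% | 21% |

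These figures describe one test on one marker and isolate the sex component. Age and weight may act in other directions, and the document does not fix the net bias.

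**3. LDH and electrolytes**

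The document gives no value for either, so there is nothing to compute. The point rests on the row assignment in Table 1 and on general physiology.

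**4. Symptom-severity groups**

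The Introduction says long COVID symptoms affect women disproportionately. The unadjusted analysis of variance could therefore meet the same sex effect, but the article gives no sex split by severity, so its size cannot be shown.

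**The case against.** The strongest reply is that Table 1 is a list of separate metrics. Nothing in Study outcomes or the Statistical plan sets a composite, a threshold or a rule that one abnormal marker makes an organ injured. LDH sits beside four other blood markers and two hepatic MRI metrics, and creatinine sits beside renal T1. The primary objective in the Introduction is led by MRI. This stands. A reader might infer that liver injury would be falsely declared at some calculable rate, or that a low creatinine would count as a healthy kidney. The document supports neither. An assumed LDH excess in hospitalised patients gives only the chance that LDH differs between groups, and the article offers nothing to anchor that excess.

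Second, derived variables and covariates are often left to an analysis plan, which is not shown. The absence of eGFR from a condensed article is therefore no fault in itself. But the article does state the row assignments and the unadjusted tests, and those are what is questioned here.

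Third, muscle loss after severe illness has little direct support in Table 3: patients are heavier than controls, and only 8% were in intensive care. The creatinine concern therefore rests mainly on the sex and age imbalance. eGFR from creatinine, age and sex also contains no muscle term, and an unadjusted comparison of it would keep the age imbalance. Replacing creatinine with eGFR would not be enough alone.

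Fourth, AST is also found in muscle and is not singled out here. That is fair. The case for relabelling is clearest for LDH, and the same caution applies when AST is interpreted.

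**Conclusion.** The point holds as one of outcome labelling and unadjusted comparison, and it is minor. Three entries among the primary organ-injury outcomes can lead a group difference to be attributed to the wrong organ, and for creatinine can mask a renal difference. The imbalance in sex, age and weight comes from the article's own Table 3. The creatinine shift of 1.4 to 2.7 µmol/L, and the loss of power that goes with it, depend on the assumed sex gap and SD and cover sex only. The LDH and electrolyte parts rest on general knowledge and have no size that the document can supply. No stated number in the article changes.

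**What to change.** - In Table 1, take LDH out of the hepatic row and report it as a non-specific marker of tissue damage.
- Remove electrolytes as a renal injury outcome. They can still be reported descriptively.
- Compare kidney function as creatinine, or as eGFR derived from creatinine, in a regression model adjusted for age and sex, for both the patient–control and the symptom-severity comparisons.
- Add MRI muscle volume as a further covariate in a sensitivity analysis, naming beforehand whether the third-lumbar or the thigh measure is used. Muscle volume was measured after infection and may itself have been changed by the illness, so it belongs in a sensitivity analysis rather than the main model.

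The cost is a change of table wording, slightly more analysis work and a shorter list of organ-injury markers. All the data needed are already in the study's data collection.

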## Introduction

The coronavirus disease (COVID)-19 pandemic has caused significant worldwide death and disability, particularly prior to the widespread availability of vaccine. Since the start of the pandemic, there have been seven waves of COVID-19 caused by evolving variants of the Severe Acute Respiratory Syndrome coronavirus-2 (SARS-CoV-2) (1, 2). In Canada, the province of Alberta, a region with 4.5 million inhabitants, has consistently had the highest seroprevalence for SARS-CoV-2 and in November 2023 approximately 85% had evidence for prior infection (3). However, the immediate health risk from acute infection has been low with a hospitalization rate of 5.5% and death in 1% (4).

While the short-term prognosis of COVID-19 is excellent, the intermediate and long-term health risks are of greater concern. A 2022 national survey found that approximately 17% of Canadians with COVID-19 report persistent symptoms lasting greater than 12 weeks, a syndrome referred to as long COVID or post COVID condition (5, 6). Symptoms are often characterized by fatigue, shortness of breath and/or cognitive impairment, with a disproportionate effect in women (5). Among affected individuals, 47% reported symptoms lasting at least 1 year and 21% described symptoms that often or always limited daily activities. The national survey also found that 27% of patient with SARS-CoV-2 developed long COVID following the Alpha variant infection compared to 13% with the Omicron variant (5).

Furthermore, population health studies have shown that COVID-19 confers a 50–70% excess risk of incident cardiovascular disease and diabetes mellitus in the first 12 months (7, 8). These health risks appear greater in patients with long COVID (9). The mechanism(s) responsible for long COVID and the increased cardiometabolic risk are not well understood and there is a lack of high-quality evidence-based studies guiding management.

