The prevailing etiologic mechanisms proposed for long COVID include immune dysregulation, autoimmunity and immune imprinting, endothelial dysfunction and thrombosis, impaired neurological signaling and effects on the host microbiome (10). However, knowledge on pathogenesis remains limited and there is an important unmet need for rigorous preclinical and clinical studies in long COVID. Given the systemic (i.e., multi-organ) nature of both acute phase COVID-19 illness and long COVID, knowledge has been gained from whole body imaging. Magnetic resonance imaging (MRI) is a safe (non-ionizing radiation), non-invasive imaging technique that provides detailed information on tissue changes including injury. MRI has been used as an alternative to computed tomography for the characterization of pulmonary disease following severe COVID-19 pneumonia (11). MRI derived measures of visceral adipose tissue and liver fat are also strongly associated with risk of hospitalization from COVID-19 independent of body mass index (12). Whole body MRI-based studies of patients with recovered COVID-19 have identified subclinical multi-organ involvement (13–15). In an MRI study of 201 patients with long COVID, mean age 45 years, organ damage was identified in 70%, including the pancreas in 45%, liver in 29% and heart in 24% (14). In this study, MRI evidence of organ impairment was defined as a non-contrast T1 time (longitudinal relaxation time) greater than normal reference values. Several cardiac MRI based studies of patients with recovered COVID-19 have found evidence of subclinical myocardial inflammation (16–18), however, the clinical significance of this finding is not well established.

We undertook a multicenter, prospective study of patients in Alberta with recovered COVID-19 from October 2020 to August 2021 to characterize symptom burden, functional impairment and end-organ damage by MRI. We hypothesized that the extent of tissue injury on MRI would be associated with patient reported disability and objective measures of functional performance.

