Our primary objective was to comprehensively apply multi-system MRI to assess the presence and extent of organ injury (heart, lungs, brain, abdominal viscera and skeletal muscle) among patients with recovered COVID-19 and compare these findings between patients with moderate to severe symptoms, minimal symptoms, and healthy controls without prior infection. As a secondary objective, we also sought to characterize imaging and circulating biomarkers with the potential to exacerbate cardiovascular health. Additionally, we incorporated opportunistic supplementary studies to explore the impact of COVID-19 on energy metabolism and patient’s perspectives.

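### The only stated patient-control test for visceral and hepatic fat is unadjusted, so it cannot separate adiposity present before infection from an effect of COVID-19

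*Protocol article*

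**What the plan says.** Under Study outcomes, "Secondary outcomes include imaging and circulating biomarkers of cardiovascular health (Table 2"). The cardiometabolic MRI cell of that table reads "Visceral adipose tissue Hepatic fat Intramuscular fat Intermuscular fat". The secondary objective in the Introduction is to "characterize imaging and circulating biomarkers with the potential to exacerbate cardiovascular health".

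The Introduction also reports, from earlier work, that "visceral adipose tissue and liver fat are also strongly associated with risk of hospitalization from COVID-19 independent of body mass index". It gives a provincial hospitalisation figure of 5.5% ("the immediate health risk from acute infection has been low with a hospitalization rate of 5.5").

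For patient-control comparisons of continuous variables, the Statistical plan names a "two sample t-test or Mann–Whitney U test used for continuous variables, as appropriate", with a p "value less than 0.05 will be considered significant for all tests". Adjustment appears in one place only, the multivariable Cox model of clinical outcome ("after adjustment for baseline risk").

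On selection:
- Study design describes controls matched on age and sex.
- Participant selection says that hospitalised cases were sought out, prospectively at one hospital and retrospectively through the health authority. Controls with cardiovascular disease or risk factors were excluded. No such exclusion is stated for patients.

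The Abstract places the patients' assessment at 3 to 6 months after infection. No scan before infection is described.

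**The concern.** The protocol's own background makes visceral and liver fat correlates of becoming ill enough to be admitted. The cohort is then enriched for admitted patients, and the same two measures are compared with controls who were screened to be free of cardiovascular risk factors. With imaging only after infection and no adjustment, a higher mean in patients could be fat that was there before, fat that came after, or a by-product of how the controls were chosen.

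At stake is the interpretation of the cardiometabolic imaging part of the secondary objective. The Abstract and Discussion look to the study for treatment targets that include cardiovascular risk after COVID-19. An unadjusted significant difference could be taken as support for that without being able to supply it.

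**Working it through.** The plan gives no figure to reproduce for this contrast; the sample size was set empirically, with no effect size or power.

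**Inputs from the document**
- Group sizes (Table 3): 215 patients, 133 controls.
- Hospitalised (Table 3): 59. Never hospitalised: 215 − 59 = 156.
- Regional hospitalisation rate (Introduction): 5.5%.
- Weight, mean (SD) (Table 3): 83 (20) v 72 (13) kg. Height: 168 v 170 cm.
- Female (Table 3): 65% v 51%. Mean age: 51 v 47 years.
- Significance level 0.05, taken as two-sided (the plan does not say).

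**Step 1. Over-sampling of hospitalised patients alone**

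Hospitalised share: 59/215 = 0.274. Excess over the province: 0.274 − 0.055 = 0.219.

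Assumption (not in the documents): before infection, patients who were later hospitalised carried D = 0.5 to 1.2 SD more fat than the others.

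Shift in the patient mean = 0.219 × D:
- D = 0.5: 0.11 SD
- D = 1.2: 0.26 SD

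Standard error of a standardised difference: √(1/215 + 1/133) = 0.110. The noncentrality is shift/0.110, that is 0.99 and 2.39. The chance of p<0.05 with no effect of infection, from the noncentral t distribution on 346 degrees of freedom:

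| D (assumed) | Shift (SD) | Chance of p<0.05 |
|---|---|---|
| 0.5 | 0.11 | 17% |
| 0.8 | 0.18 | 35% |
| 1.0 | 0.22 | 51% |
| 1.2 | 0.26 | 66% |

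The nominal rate is 5%.

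**Step 2. What the observed weight gap could add**

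Difference: 83 − 72 = 11 kg. SE = √(20²/215 + 13²/133) = 1.77, so the 95% CI is 11 ± 1.96 × 1.77 = 7.5 to 14.5 kg. The pooled SD is 17.7 kg, so the standardised gap is 11/17.7 = 0.62. BMI from the group means: 83/1.68² = 29.4 v 72/1.70² = 24.9 kg/m².

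Assumption (not in the documents): a fat measure correlates r with weight. The expected gap in fat is then r × 0.62.
- r = 0.3: 0.19 SD, 39% chance of p<0.05
- r = 0.5: 0.31 SD, 80%
- r = 0.7: 0.44 SD, 98%

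This is an upper scenario. It treats the whole 11 kg as present before infection, and the documents give no weight from before infection. It also includes whatever part comes from excluding controls with risk factors. Steps 1 and 2 overlap and must not be added.

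**Step 3. Precision after restriction**

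With 156 patients and 133 controls the standard error is √(1/156 + 1/133) = 0.118, against 0.110 with all 215: about 7% larger.

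**The case against.** The strongest reply is that the protocol makes no causal claim about fat. The objective is to characterise markers of later risk, Table 1 leaves every fat measure out of organ injury, and the symptom-severity analysis is confined to measures of organ injury. The Statistical plan states its two-sample tests in general terms and does not name the fat measures. Part of a remedy is already planned, since all imaging parameters enter the Cox models as predictors of 12-month events. A full analysis plan, not shown, might also adjust.

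Much of this stands, and it limits the point. It does not remove it: the fat measures are listed as outcomes, controls were scanned too, and the only patient-control method stated for continuous variables is unadjusted.

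Four stronger readings are tempting but not supported:
- *The result is a foregone conclusion.* The 80% to 98% figures need the whole weight gap to predate infection. Part may be control selection or later gain. The hospitalisation mechanism alone gives 17% to 66%, and 156/215 = 73% of patients were never hospitalised.
- *All four fat measures are affected on the protocol's own evidence.* The Introduction's statement covers visceral and liver fat only, and concerns hospitalisation rather than infection.
- *The measures should be reclassified as risk factors from before infection.* Scans at 3 to 6 months cannot carry that label; it would replace one unsupported direction with the opposite one.
- *Adjusting for weight settles it.* Weight in Table 3 describes patients already infected, so adjustment could remove part of a real effect. The Introduction also says the link with hospitalisation is independent of BMI, so body size alone need not remove the bias.

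**Conclusion.** The concern holds for two secondary imaging measures, visceral adipose tissue and hepatic fat. As the Statistical plan stands, their patient-control contrast cannot distinguish prior adiposity from an effect of infection, and a difference is plausible with no such effect. The part attributable to over-sampling hospitalised patients is about 0.11 to 0.26 SD, with a 17% to 66% chance of nominal significance. That range depends entirely on the assumed 0.5 to 1.2 SD gap before infection. The weight imbalance could make the bias larger, by an amount the documents do not allow one to fix.

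The point does not touch the organ-injury outcomes in Table 1 or the planned use of imaging measures as predictors of 12-month events. A reader might infer that the protocol attributes body fat to COVID-19; it does not say so. The fault lies in the planned comparison and in how its result could be read.

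**What to change.** Keep the measures in Table 2. In the Statistical plan, for visceral adipose tissue and hepatic fat:

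1. Replace the unadjusted patient-control test with a regression adjusted for age and sex. The groups differ on both despite the intended matching (65% v 51% female; mean age 51 v 47 years).
2. Repeat it in the 156 never-hospitalised patients against the controls.
3. Add a sensitivity analysis that also includes weight and height, noting that weight was measured after infection.
4. State that the result is an association whose direction cannot be determined, because there is no scan before infection and controls were selected to be free of cardiovascular risk factors.

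Age and sex adjustment alone does not deal with prior adiposity; items 2 to 4 address that, and only in part.

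The cost is a few sentences in the Statistical plan and a little more analysis, with no new data. The restricted analysis loses some precision (standard error about 7% larger before adjustment) and leaves out the most severely ill, in whom any effect of infection might be greatest. The comparison will also be less striking.
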